**Figure 1 figure1:**
[figure not shown]
Daily drinking diary.

### Triage Module

The triage module is a short module intended to introduce clients to the RPT program and the drinking diary. All participants in the e-RPT and face-to-face groups will complete this module before starting their respective treatments.

### e-RPT

Participants in the e-RPT group will receive 10 predesigned online modules per week on the OPTT platform. Each module consists of approximately 30 slides and should have an estimated completion time of 45 minutes. At the end of each module, participants will be assigned homework to be completed before their next module is assigned. The therapists will submit personalized feedback by using session-specific therapy feedback templates. These structured templates standardize the quality of feedback across different patients and therapists. In previous studies, therapists have been able to effectively use these templates to prepare feedback in approximately 15-20 minutes [30].

This e-RPT program will focus on teaching essential cognitive and behavioral skills such as identifying maladaptive thought processes, increasing engagement in day-to-day activities, and developing strategies to reduce alcohol consumption. The content of the sessions is outlined in Table 1.

**Table 1 table1:** The program outline and session summary for the 10-week web-based and face-to-face relapse prevention program.

Session number	Session subject
1: Understanding addiction	Introduces relapse prevention and what to expect from the course. The session explains what addiction is, including the symptoms, signs, consequences, and different types of addiction. Participants will create a SMART goal that they will try to achieve throughout the program. They will also share their personal experiences with addiction.
2: Exploring and strengthening your motivation	Focuses on the 5 stages of motivation and the role of motivation in relapse prevention. Helpful techniques are discussed to help them reflect on and boost motivation throughout their recovery journey. Participants will create a pros and cons list about stopping alcohol use and reflect on different aspects of their ability to stop using alcohol.
3: Triggers	Describes what triggers are and how to recognize them, including both internal and external triggers. This session also provides strategies to handle triggers through avoidance and careful planning. Participants will learn to identify their triggers and to be prepared for them if encountered.
4: Handling cravings and signs of relapse	Presents skills for dealing with cravings as well as identifying and preventing a potential relapse. For instance, applying distraction methods during stressful situations decreases their urge to consume alcohol. Participants will also identify their warning signs by reflecting on previous relapse experiences.
5: The 5-Part Model	The 5-Part Model will be explained, which highlights the importance of differentiating between our thoughts, feelings, physical reactions, and behaviors in stressful situations. Participants will complete the 5-Part Model using an example from their lives.
6: The Thought Record—Part 1	Introduces the thought record and its relation to cognitive restructuration to highlight the connection between feelings, behaviors, and thoughts. This session focuses on the first 3 columns of the Thought Record (out of 7 columns). The first 3 columns include the situation, followed by the feelings and automatic thoughts associated with the situation. Participants are asked to complete the first 3 columns of a thought record for a stressful situation they experienced within the past week.
7: The Thought Record—Part 2	This session continues with the remaining 4 columns of the Thought Record, including gathering evidence in support of and against the identified automatic thoughts and finding alternative and balanced thoughts after examining the evidence. Participants will learn to challenge irrational thoughts using the thought record. They will also learn how to replace these irrational thoughts with more balanced and helpful ones. Participants have to complete a full thought record of a stressful situation related to their AUD within the past week.
8: Thinking errors and the Activity Record	Explores irrational thinking and common thinking errors. This session also presents and highlights the importance of the Activity Record, a tool designed to record and plan weekly activities. Participants are asked to complete an activity record for an entire week.
9: Mindfulness and breathing techniques	Presents mindfulness, breathing techniques, and other helpful skills to reduce urges and cravings associated with alcohol and to promote increased awareness. Participants are asked to incorporate one or more of these practices into their daily routines for a week and to reflect on how these practices made them feel. Participants will also identify which, if any, practices they found to be most effective.
10: Review	This session is a review of the program. It summarizes all of the useful tools and techniques for relapse prevention that were described throughout the program. Participants are asked to reflect on the activities that they found to be the most effective throughout the sessions.

### Face-to-Face RPT

Participants in the face-to-face intervention will meet with their therapist weekly through videoconferencing on Microsoft Teams [38]. During these 1-hour sessions, therapists will follow the same 10-week structure and content as e-RPT (Table 1). In contrast to e-RPT, where homework is written web-based by the therapist, the homework for the face-to-face sessions will be reviewed with the participant during the live session. At the end of each session, participants will receive the same homework and feedback as the e-RPT condition.

### Training

Therapists for both e-RPT and face-to-face RPT will consist of research assistants who are trained in RPT and writing feedback. All therapists are trained by the PI, who is an expert in the electronic delivery of psychotherapy [30,39,40]. During training, the PI will closely guide the therapists through their first patient (assigning modules, reviewing homework, writing feedback, and conducting face-to-face sessions). All therapists will be supervised by the PI to ensure the quality and reliability of the treatment programs. To ensure the quality of the feedback, therapists will practice writing it using structured templates. All face-to-face sessions and feedback will be reviewed with the PI before being sent to the participants.

### Outcome Measures

The primary objective of this study will be to determine if e-RPT has similar effectiveness to face-to-face RPT at reducing alcohol consumption and preventing relapses. This study defines relapse as either the consumption of at least 2.5 oz. of pure ethanol, which is around 4 and a half standard drinks (Canadian guidelines for standard drinks: 12 oz of beer with 5% ethanol, 12 oz of cider with 5% ethanol, 5 oz of wine with 12% ethanol, and 1.5 oz of spirits with 40% ethanol) [41,42] on one occasion or hospitalization because of alcohol drinking [43]. Therefore, to determine the effectiveness of this program, daily alcohol consumption will be recorded in a drinking diary accessible through OPTT. This diary will ask the participants to report how many drinks they consumed on each day of the week, where they had those drinks, with whom, and if their alcohol consumption resulted in hospitalization (Figure 1).

The study will also determine whether e-RPT and face-to-face RPT have a beneficial effect on self-efficacy, quality of life, resiliency, coping behaviors, and depressive symptomatology. These metrics will be assessed through the following scales: Situational Confidence Questionnaire (SCQ-100) [44], 14-item Resilience Scale (RS-14) [45], Coping Behaviors Inventory (CBI) [46], Patient Health Questionnaire (PHQ-9) [47], and Quality of Life Enjoyment and Satisfaction Questionnaire—Short Form (Q-LES-Q-SF) [48]. These assessment scales will be completed at study entry (baseline), amid the program (week 5), and post treatment (week 10). After the treatment period, we will conduct follow-up assessments with all our outcome measures at 3, 6, and 12 months. The amount of time that e-RPT therapists spend writing feedback compared to the 1-hour face-to-face session will be used as a measure of therapists’ time efficiency and will be tracked on the OPTT platform.

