Therefore, this study proposes the development, study, and implementation of an e-RPT program for the management of AUD. The proposed program could be a viable solution to address the potential accessibility, stigma, and financial issues presented by traditional in-person therapies [32]. Thus, the primary objective of this study is to compare the efficacy of a secure e-RPT program to face-to-face RPT to decrease relapse rates in patients with AUD. Based on the evidence comparing face-to-face and web-based psychotherapies in other disorders, we hypothesize that both face-to-face RPT and e-RPT will have similar effectiveness in AUD symptom management, reducing alcohol consumption, and lowering relapse rates [33,34]. The secondary objective is to assess the effects of online treatment on quality of life, self-efficacy, resilience, and depressive symptomatology. The tertiary objective is to evaluate cost-effectiveness by comparing the amount of time an e-RPT therapist spends with each patient to the therapists administering face-to-face RPT. The results of this study will supplement the available literature and aid in the development of clinical recommendations for the management of AUD.

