### Data Analysis

The data will be initially assessed for outliers, missing, and nonsensical variables. These variables will not be imputed, since they will be handled as missing. Similar studies that involved CBT and e-CBT demonstrated a dropout rate of up to 40% for both conditions once the study concluded [49]. Thus, this study will intentionally oversample the experimental and control groups to account for this dropout rate. Considering the effect size for face-to-face RPT reported by Harada et al [50] (2021) for CBI (effect size=0.65), a significance level of α=.05 and a power of 0.90, a sample size of 60 (30 per arm) would be sufficient to detect substantial changes from our interventions [51]. As this is the first study aiming to establish an e-RPT program for AUD, this sample size calculation relies on data from face-to-face RPT and takes into account the established effectiveness of online psychotherapy compared to face-to-face psychotherapy [30].

The analysis will begin by examining the data for missing, nonsensical, and outlying variables. The data will then be analyzed on a per-protocol basis, excluding missing data, and with intention-to-treat analysis to assess the clinical effects of the program on participants who dropped out prematurely. All calculations will be done using a 2-tailed significance level of α=.05, except for when a Bonferroni correction is needed. The demographic information of program completers and program dropouts will be compared using independent sample *t* tests to identify possible differences. A 2 by 3 repeated measures ANOVA of the primary (daily drinking and relapse) and secondary (SCQ-100, Q-LES-Q-SF, RS-14, CBI, and PHQ-9) outcomes will be conducted to test for the effects of the interventions (e-RPT or face-to-face RPT) throughout the 10-week treatment (0, 5, and 10-week assessment points). Linear regression (for continuous outcomes) and binomial regression analysis (for categorical outcomes) will be used to identify variables associated with outcome measures. Additionally, OPTT will collect usage statistics (ie, number of logins per day, amount of time spent logged in) and compare them to face-to-face metrics (ie, attendance to weekly 1-hour face-to-face sessions) to determine cost and time savings between the 2 programs. All statistical analyses will be conducted using IBM SPSS Statistics for Mac (version 24; IBM Corp).

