## Discussion

This is a protocol for an RCT that aims to establish a novel e-RPT program to improve the mental health of patients with AUD. This program will teach effective coping techniques to maintain abstinence and reduce the risk of a relapse by applying the widely validated principles of CBT and relapse prevention [12,24,31,32,50]. Supporting the structure and design of this program, this study will apply the evidence gathered by Alavi et al [30,39,40] on the efficacy of e-CBT in managing other psychiatric disorders. Thus, this study hypothesizes that this novel e-RPT program will have a similar effectiveness as face-to-face RPT at maintaining long-term abstinence and reducing the risk of experiencing a relapse.

Psychosocial interventions are one of the most commonly used methods for the treatment of mental health disorders [18]. CBT is one of the most-studied approaches for treating AUD and involves one-on-one sessions between the patient and therapist [19]. These sessions work on overcoming cravings for drinking alcohol by developing strategies that help people abstain from consuming alcohol when cravings occur. When targeted to prevent or reduce the risk of relapses after an initial alcohol reduction program, this CBT approach becomes RPT. RPT involves addressing coping skills to decrease the risk of relapse [21,50]. Additionally, both interpersonal and intrapersonal factors are addressed so that patients can develop the skills necessary to aid in preventing relapse. For instance, through the development of coping mechanisms to respond effectively to stressful situations that otherwise could have led to relapse [12,50]. However, despite these benefits, there are many obstacles to receiving face-to-face psychotherapy, such as financial issues and logistical problems.

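### The primary question is whether the two programs are similarly effective, but the plan fixes only a two-sided difference test, with no margin or confidence-interval rule, so it cannot establish similarity

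*Protocol article*

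**What the plan says.** Outcome Measures gives the primary objective as "to determine if e-RPT has similar effectiveness to face-to-face RPT at reducing alcohol consumption and preventing relapses". The Introduction hypothesises that "both face-to-face RPT and e-RPT will have similar effectiveness in AUD symptom management, reducing alcohol consumption, and lowering relapse rates", and the Discussion repeats that "this novel e-RPT program will have a similar effectiveness as face-to-face RPT at maintaining long-term abstinence" is expected. The wording is not uniform. The Abstract's objective and another sentence in the Introduction describe the aim neutrally, as a comparison of the efficacy of the two programs.

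Data Analysis fixes how the arms are compared: "All calculations will be done using a 2-tailed significance level of α=.05, except for when a Bonferroni correction is needed", and "A 2 by 3 repeated measures ANOVA of the primary (daily drinking and relapse) and secondary" outcomes over weeks 0, 5 and 10. The regressions have a different role; they "will be used to identify variables associated with outcome measures". Both per-protocol and intention-to-treat analyses are planned. The sample size of 60 (30 per arm) rests on an effect size of 0.65 for the Coping Behaviors Inventory (CBI), a secondary outcome, at α=.05 and power 0.90. It is described as enough to detect changes from the interventions. The article states no margin, no confidence-interval rule and no other criterion for concluding similarity.

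**The concern.** Whether two treatments are similarly effective is an equivalence or non-inferiority question. It is answered by showing that the difference lies within a limit set in advance. The planned ANOVA asks the opposite question: whether the data contradict a difference of exactly zero. A significant result would count against similarity. A non-significant one would say only that the data could not tell the arms apart, which happens readily in a small trial and more readily with each participant lost.

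At stake is the main conclusion. With no other rule on the page, a non-significant comparison is the only result that could be taken as support for the hypothesis. A web-based program that was materially worse could then be described as similar to therapist-led sessions. The article's closing paragraph looks ahead to large-scale implementation.

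**Working it through.** **Inputs from the article.** 30 per arm (Procedure; Data Analysis). Dropout of up to 40% (Data Analysis), which leaves 30 × (1 − 0.40) = 18 per arm at worst. Two-sided α of 0.05. Effect size 0.65, power 0.90. Relapse of 60% to 80% after 3 months of treatment (Introduction, citing an outside study).

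**Assumptions of this check.** A two-group comparison at one time point; a true deficit of 0.5 SD as an example; baseline-to-outcome correlations of 0.3 to 0.7. The article gives none of these.

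**1. The plan's own figure.** A between-arm comparison with effect size 0.65, two-sided 0.05 and 90% power needs 2 × (1.960 + 1.282)² / 0.65² ≈ 50 per arm, so 100 in total before dropout. A within-arm paired t test, two-sided, needs 27 per arm, or 27 / 0.6 = 45 with dropout. Neither gives 30 per arm after allowing for 40% dropout, and the text does not say which comparison was meant. For this point it is enough that the calculation concerns detecting change on the CBI. It does not concern excluding a margin on drinking or relapse.

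**2. Precision in SD units.** The 95% half-width is t(0.975, 2n − 2) × √(2/n).
- n = 30: 2.002 × 0.2582 = 0.52 SD
- n = 18: 2.032 × 0.3333 = 0.68 SD

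In this comparison at 18 per arm, even an observed difference of zero would not exclude 0.65 SD, the effect size that the protocol takes from face-to-face therapy.

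**3. Precision for relapse.** The 95% half-width is 1.96 × √(2p(1 − p)/n), with the same p in both arms.

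| Relapse p | n = 30 | n = 18 |
|---|---|---|
| 60% | 24.8 points | 32.0 points |
| 70% | 23.2 points | 29.9 points |
| 80% | 20.2 points | 26.1 points |

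**4. How often a real deficit would be non-significant.** For a true deficit of 0.5 SD, the two-sample t test has power 0.478 at 30 per arm and 0.308 at 18. It is therefore non-significant 52% and 69% of the time.

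**5. Sensitivity to the repeated measures.** For change from baseline, the SD of the change is √(2(1 − ρ)) times the single-time SD, so the standardised deficit is 0.5 / √(2(1 − ρ)).

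| Correlation ρ | SD factor | Standardised deficit | Non-significant, n = 30 | Non-significant, n = 18 |
|---|---|---|---|---|
| 0.7 | 0.775 | 0.645 | 31% | 53% |
| 0.5 | 1.000 | 0.500 | 52% | 69% |
| 0.3 | 1.183 | 0.423 | 64% | 77% |

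The half-widths in step 2 scale by the same factor. At 30 per arm they run from 0.517 × 0.775 = 0.40 to 0.517 × 1.183 = 0.61 SD; at 18 per arm, from 0.677 × 0.775 = 0.52 to 0.677 × 1.183 = 0.80 SD.

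**The case against.** **Non-significance as the planned criterion.** A reader might infer that the investigators mean to report a non-significant result as similarity. The article nowhere says so. What stands is a risk: an objective with no rule for answering it, next to a test that cannot answer it.

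**The neutral wording.** The Abstract and part of the Introduction speak only of comparing efficacy, and the Results section hypothesises only that both programs will help. A two-sided comparison fits those sentences. This does not remove the mismatch, because Outcome Measures and the hypotheses are explicit about similarity. It does show that an estimation aim would already agree with part of the article.

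**The sample size.** It is tempting to call 60 a between-arm difference calculation. The text speaks only of changes from the interventions, which may mean change within an arm, and 60 does not reproduce as a between-arm number. The safe statement is that it was not derived from a margin.

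**The illustrations.** They are not the operating characteristics of the planned ANOVA, whose precision depends on an unstated correlation. Eighteen per arm is the worst case. The 60% to 80% relapse range comes from a cited study and may not fit a trial of mild to moderate disorder that excludes heavier recent drinkers. Assigning one end of that range to each arm would suggest a 20-point deficit for which the documents give no basis. All of this stands, which is why ranges are shown.

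**What might be left to an analysis plan.** A margin could be added there. But the article itself fixes the objective, the test and its sidedness, and these conflict. Planning both per-protocol and intention-to-treat analyses suits a non-inferiority question, but neither shows similarity without a margin.

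**Conclusion.** The point holds. The similarity objective has no margin or decision rule, and the fixed analysis is a two-sided test of no difference, so the plan as written cannot answer its primary question. This follows from the text and needs no numerical assumption.

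The numbers indicate scale only. For a two-group comparison at one time point, the 95% interval is about ±0.52 SD at 30 per arm and ±0.68 SD at 18. For relapse of 60% to 80% it is about ±20 to 25 points and ±26 to 32 points. A true deficit of 0.5 SD would be missed about 52% to 69% of the time. As a change from baseline, with assumed correlations of 0.7 to 0.3, it would be missed 31% to 64% of the time at 30 per arm and 53% to 77% at 18. In each case fewer completers make a non-significant result more likely.

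The documents do not support the further inference that misreporting a null result is planned. Whether change over time can be credited to e-RPT without an untreated arm is a separate question and carries no weight here.

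**What to change.** 1. Restate the primary aim as estimation, in line with the neutral comparison wording already in the Abstract and Introduction, and align Outcome Measures and the hypotheses with it.
2. For each stated primary outcome, relapse and daily drinking, report the between-arm difference (e-RPT minus face-to-face) with its 95% confidence interval at a named time point. The planned ANOVA ends at week 10.
3. Add a rule such as: *A non-significant difference will not be reported as similar effectiveness. Similarity may be concluded only if the 95% confidence interval excludes a margin that was justified and fixed before any outcome data were compared by arm.* The condition is worded this way because the Discussion says that allocation cannot be concealed.
4. State the precision that 60 participants give, with and without 40% dropout, and the assumptions behind it.

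This costs wording and an added interval estimate; no new data are needed. The drawback is that the trial will probably be unable to claim similarity. A confirmatory non-inferiority claim would need its own justified margin and a sample size built on it, and is not part of this change.

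### Relapse, a primary outcome, has one named source for both its parts, a self-completed diary with unimputed gaps, so events can be selectively lost

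*Protocol article*

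**What the plan says.** Outcome Measures in the protocol article gives a two-part definition: "This study defines relapse as either the consumption of at least 2.5 oz. of pure ethanol" as the first part, completed by "on one occasion or hospitalization because of alcohol drinking". Data Analysis lists daily drinking and relapse as the primary outcomes.

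The source for both parts is the same. Outcome Measures states that "daily alcohol consumption will be recorded in a drinking diary accessible through OPTT". It goes on: "This diary will ask the participants to report how many drinks they consumed on each day of the week", and the same form asks "if their alcohol consumption resulted in hospitalization". The five rating scales scheduled at baseline, week 5 and week 10 cover self-efficacy, resilience, coping, depression and quality of life. None is assigned to relapse or admission. No hospital record, clinician report or collateral report is named.

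On follow-up, the same section says "we will conduct follow-up assessments with all our outcome measures at 3, 6, and 12 months".

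On gaps, Data Analysis says of outlying, missing and nonsensical variables: "These variables will not be imputed, since they will be handled as missing". It then states: "The data will then be analyzed on a per-protocol basis, excluding missing data, and with intention-to-treat analysis". The same section expects dropout of up to 40% in both conditions.

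**The concern.** Whether a relapse is seen depends on the participant filling in the diary around the time it happens. Someone drinking heavily, or in hospital because of drinking, is plausibly less likely to do so. If the entry is not made, the event becomes a missing value and stays one. The missingness then depends on the outcome itself, and excluding missing data gives a relapse rate that is too low.

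Two things are at stake. The first is the absolute relapse rate in each arm, which the trial will want to report and compare with the literature. The second is the comparison between arms. If diary completion differs between e-RPT and face-to-face RPT, the arm with less complete diaries appears to relapse less. The trial's hypothesis is that the two formats perform similarly, so a spurious difference, or one that hides a real difference, bears directly on its conclusion.

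**Working it through.** The article gives no figure for diary completion or for relapse under this definition, so there is no stated figure to reproduce. The sample size rests on a coping scale and does not enter here. The calculation below illustrates size only.

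**Inputs**
- True relapse rate p: 60% to 80%, the span quoted in the Introduction for people with AUD 3 months after treatment. Using it for this mild to moderate sample is an assumption.
- Share with missing relapse status m: 40%, the upper dropout figure in Data Analysis. Equating study dropout with missing relapse status is an assumption.
- Odds of missing data in relapsers relative to non-relapsers, R: 1, 2 or 4. These are assumed.

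**Formulas**
- Let m0 be the missing fraction in non-relapsers and m1 that in relapsers.
- m1/(1 − m1) = R × m0/(1 − m0)
- (1 − p) × m0 + p × m1 = m
- Observed rate among those with data = p × (1 − m1)/(1 − m)

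**Understatement within an arm, m = 40%**

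| True p | R | m0 | m1 | Observed | Understated by |
|---|---|---|---|---|---|
| 60% | 1 | 40.0% | 40.0% | 60.0% | 0 |
| 60% | 2 | 30.3% | 46.5% | 53.5% | 6.5 points |
| 60% | 4 | 21.5% | 52.3% | 47.7% | 12.3 points |
| 70% | 2 | 28.8% | 44.8% | 64.4% | 5.6 points |
| 70% | 4 | 19.3% | 48.9% | 59.6% | 10.4 points |
| 80% | 2 | 27.5% | 43.1% | 75.8% | 4.2 points |
| 80% | 4 | 17.4% | 45.7% | 72.5% | 7.5 points |

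Worked line for p = 70%, R = 2: 0.3 × 0.288 + 0.7 × 0.448 = 0.40, and 0.7 × (1 − 0.448)/0.6 = 0.644.

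The range for R of 2 to 4 is therefore about 4 to 12 points. If missingness is unrelated to relapse (R = 1), there is no understatement. At the extreme, if everyone missing had relapsed, a true 70% would be seen as (0.70 − 0.40)/0.60 = 50%.

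**Effect on the comparison, true rate 70% in both arms**
- 40% missing in both arms: both observed rates are equal, so the difference is 0.
- 40% versus 20% missing, R = 2: 64.4% against 67.4%, a spurious 2.9 points (before rounding).
- 40% versus 20% missing, R = 4: 59.6% against 65.4%, a spurious 5.8 points.

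In both unequal cases the arm with more missing data looks better.

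**Does the intention-to-treat analysis repair this?** Data Analysis names one for participants who leave early, but the same section rules out imputation. Keeping a participant in the analysis set does not supply a relapse status that was never observed.

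**The case against.** The strongest opposing case has four parts.

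*Other sources and diary coverage may be described elsewhere.* This is a condensed article, and the diary form (Figure 1) is not shown, so its look-back wording and any late entry are unseen. This stands as a limit. The point is that no other source is named, not that none exists. A reader might infer that a diary completed at 3, 6 and 12 months cannot see events between those visits. The text does not support that: it neither stops the diary at week 10 nor confines it to one week per visit. Coverage there is unspecified. The planned 2 by 3 ANOVA also uses only weeks 0, 5 and 10, so the follow-up gap lies outside that test.

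*The direction of any arm difference is unknown.* A reader might infer that e-RPT, having no live session, would have emptier diaries and so look better. The documents do not support this. Both arms use the same OPTT diary, introduced by the same triage module. e-RPT participants also do their modules on that platform, while face-to-face sessions run on Microsoft Teams. Completion could be higher in either arm, and the expected dropout figure is the same for both.

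*The bias is small beside sampling error.* With 30 per arm and 70% relapse, the standard error of the difference is √(2 × 0.7 × 0.3/30) = 0.118, about 12 points. This is true and limits the practical weight of a 3 to 6 point shift. It does not remove the understatement of the rates themselves.

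*The detailed missing-data rule may sit in an analysis plan.* That is possible, but an analysis rule cannot recover events that were not collected. For the same reason, lower rates obtained by counting blanks as no relapse should not be attributed to this plan: it says that gaps are treated as missing.

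**Conclusion.** The point holds as a weakness in how a primary outcome is collected. Both parts of relapse have a single named source, that source is completed by the participant, and its gaps are left missing in a trial that expects up to 40% dropout. Under-counting follows if relapsers are less likely to complete the diary, which is plausible but not documented. The size is about 4 to 12 points on true rates of 60% to 80%, resting on 40% missing relapse status and odds of missingness 2 to 4 times higher in relapsers.

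Bias between the arms needs unequal completion as well. At an assumed 40% versus 20% missing and a true 70%, it is about 3 to 6 points in favour of the arm with more missing data. Which arm that would be cannot be predicted. The text does not establish that events between follow-ups go unseen, only that diary coverage of those months is not stated.

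**What to change.** At every assessment already scheduled after baseline (weeks 5 and 10; 3, 6 and 12 months), and at withdrawal, ask both arms the same two questions:
1. Since the last assessment, was there any day on which you drank at or above the relapse threshold, and on what date was the first?
2. Since the last assessment, were you hospitalized because of drinking, and on what date?

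State one scoring rule: the diary determines relapse status for periods with entries, and the interval answer determines it for periods where the diary is blank. The dates allow an answer to be placed in one or the other. Report diary completion by arm, so that readers can judge whether it differed. State also whether the diary runs continuously between the follow-up assessments.

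The cost is two items in existing assessments, the same items at withdrawal, one sentence of scoring and one reported table row. Treatment, scheduled visits and sample size are unchanged. The downsides are that recall over an interval is less exact than daily entry, which is why it only fills gaps, that the answers are still self-report, and that participants lost to all contact remain missing.
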